#### Evaluation of Pharmacist Activity and Medication Changes

1. Chart review by a research assistant will define the number of PCP and pharmacist encounters as well as the number of pharmacist- or physician-initiated medication changes.

#### **6.4 Components of *mDAS***

*Videoconferences.* Pharmacist videoconferences 30-45 minutes in duration will be scheduled every other month or as needed. HCs will reserve videoconference appointments using an online system with dedicated days/times pharmacists are available. All patient encounters with pharmacists are remote via videoconferencing with HCs present in the home using VSee. VSee transmits personal health information securely, is low cost, and is available for use on desktop computers and mobile devices (e.g., iPads). Similar to Skype, VSee provides real-time person-to-person audio and video communications. However, it is most suitable for health-related communication, as it is FDA registered and HIPAA compliant (using 256-bit AES, Advanced Encryption Standard). VSee uses “peer-to-peer” sessions so information is not stored on a server.

Videoconferencing will follow the American Telemedicine Association practice guidelines: (1) pharmacist and patient/HC identity verification; (2) informed consent; (3) physical environment (privacy, lighting, noise); (4) education and training (pharmacist and HC); (5) alternate communication (e.g., telephone contact in case of disruption of service); and (6) documentation in UI Health EMR (by pharmacist). All study pharmacists and HCs will receive standardized training on use of videoconferencing which includes scheduling, preparing the environment (home or pharmacist office), patient education on telehealth, and documentation. We will evaluate HC and pharmacist competency. All encounters will have contingency plans in place for technology problems (e.g., inadequate signal for video streaming), including use of mobile phones for all HCs. Videoconference content includes standardized medication and disease management.

*Pharmacist Services.* Pharmacist services follow a standardized Pharmacist Management Protocol. All participating clinical sites have clinical pharmacists providing in-person disease management services and follow a similar protocol. All participating pharmacists have faculty appointments in the UIC Department of Pharmacy Practice. The UI Health system is a teaching hospital and as such, pharmacists at participating sites train an ongoing rotation of pharmacy residents and students. With the patient’s permission, residents and students may observe clinical consultations performed by the pharmacist. Residents and students will not provide any clinical care to patients and will not perform any videoconference visits. They will not have any role in this study. The clinical pharmacist reconciles medications during the first encounter with

assistance from the HC in the patient's home. Follow-up *mDAS* pharmacist activities include evaluation of medication and lifestyle adherence, reviewing home glucose and/or blood pressure monitoring log data, identifying therapeutic goals, formulating an approved plan of care, assessing for changes in medications, and documenting the plan in the EMR.

In addition, pharmacists provide education related to medication (name and purpose of medications; time, strength, and method of administration); drug interactions and side effects; goals of therapy; basic lifestyle modifications; and use of pillbox, low-literacy visual medication lists, or other adherence aids. Pharmacists educate and encourage lifestyle changes based upon ADA nutrition and physical activity guidelines. They propose medication changes based on algorithms and protocols derived from national guidelines under physician guidance. Pharmacists will have access to home glucose monitor readings during the videoconference, as well as ambulatory blood pressures obtained by the HC during home visits. Pharmacists will set the goals for A1c and blood pressure collaboratively with PCPs (e.g.,  $A1c \leq 7\%$ ) as is the case in regular clinical practice within our setting. These procedures are currently followed with clinical pharmacists in ambulatory management of complex patients with uncontrolled diabetes.

Overall, there is mixed evidence regarding the benefits of aggressive glycemic control. In the proposed study, PCPs and pharmacists will adopt the ADA approach to individualized care, where the general goal for non-pregnant adults is A1c less than 7%. They may decide upon less stringent goals for those with a history of severe hypoglycemia, limited life expectancy, advanced complications, or extensive comorbid conditions. Pharmacists routinely monitor hypoglycemic events, address prevention and review treatment. This includes three steps: (1) addressing hypoglycemia with every patient contact; (2) applying principles of appropriate therapy (education, empowerment, frequent glucose self-monitoring, flexible medication regimen, individualized goals, professional guidance); and (3) considering risk factors for hypoglycemia. In addition, pharmacists will follow the 2013 American College of Cardiology/American Heart Association guidelines for lipid management (e.g., calculating 10 year atherosclerotic cardiovascular risk to determine statin intensity).

PCPs and pharmacists communicate routinely regarding patient care and are located in the same area within the medical setting. Pharmacists review EMRs including blood test results, clinical progress notes, problem and medications lists, drug allergies, hospitalization records, and emergency room reports. Non-urgent communication and electronic progress notes from each pharmacist encounter will be sent to the PCP through inbox messaging and note forwarding within the EMR. Pharmacist progress notes include a detailed list of medications, estimated adherence levels, and home glucose/blood pressure monitoring log information.

*Health Coaches.* The study includes both African-American and bilingual/bicultural Latino health coaches representative of the communities they serve. All of our current HCs are the first person in their families to earn an undergraduate college degree, come from low-income backgrounds, and recognize the importance of cultural-based norms. All HCs have an undergraduate degree in or related to Community Health with experience conducting home visits. They receive 80 hours of standardized training/retraining beginning with diverse Latino and African-American cultures in America and the influence of poverty upon health. HCs provide culturally sensitive support and tailor based on participant personal preferences. Fundamental education in diabetes includes the Diabetes Education Empowerment Program

(DEEP) targeting literacy and cultural awareness and [name] Training Curriculum for Health Coaches. HCs shadow a clinical pharmacist to understand medication use, adherence, glucose and blood pressure monitoring, insulin injection, and medication reconciliation. On-going training is provided every two months on related topics that reinforce and expand the initial training. We provide training in videoconferencing (e.g., scheduling and practice encounters), text messaging (e.g., text application practice and standardized safety procedures), and conducting home visits in a culturally sensitive manner. HCs receive routine orientation to clinical operations and staff at their primary care locations. Standardized safety procedures related to text messaging and home visits are also addressed. [name], a consultant, provides training in motivational interviewing related to adherence. To evaluate clinical skills, the HCs will demonstrate reliable measurement of blood sugar, blood pressure, pulse, and administration of insulin (though HCs do not administer insulin to patients).

The HC component involves monthly home visits with on-going telephone support. Every other month a visit will include facilitation of the pharmacist videoconference, with the patient spending an additional time with the HC afterwards for reinforcement. HC visits including pharmacist videoconferencing will last 60-90 minutes total, while the HC visits without pharmacist involvement will last 30-45 minutes.

The HCs work with the pharmacist to evaluate adherence (e.g., check fill and expiration dates), assist in medication reconciliation, review home glucose and/or blood pressure monitoring data, and provide reinforcement of proper medication use. Finally, HCs debrief patients after pharmacist encounters to reinforce and clarify recommendations and plans. HCs and pharmacists will communicate with each other between videoconference encounters by phone or secure e-mail as needed to coordinate efforts. HCs provide pharmacists with valuable insights into culturally-influenced lifestyle issues and health beliefs.

Home visits include the HC, patient, and family members or co-residents as appropriate and permitted by the patient. This is particularly helpful when someone else prepares meals for the patient. HCs address nine critical content areas over the course of the one-year intervention: relationship building, diabetes education, medication reconciliation, adherence barriers, engaging social support, navigating the healthcare system, exploring emotions, movement or physical activity, and nutrition. HCs evaluate key points in each content area which guides their work with each patient. HCs can check blood pressure and blood sugar to share with the pharmacist and other providers. HCs will document summaries of all patient communication in the EMR through remote access and forward electronically to PCPs and pharmacists.

HCs will attend to lifestyle and medication adherence issues by identifying and tracking barriers, problem solving, goal-setting, and providing supportive accountability. Using motivational interviewing techniques, HCs help patients identify diabetes-related goals and create action plans. Many of our patients are socially isolated. An important HC role is to identify extended family, friends, or neighbors for support. HCs engage support for tangible tasks tailored to the patient and directed at positively impacting adherence.

Diabetes education is facilitated by our culturally appropriate multimedia education iBook, *Living Well with Diabetes/Viviendo Bien con Diabetes* (LWD). This iBook is available in English and Spanish and targets African-Americans and Latinos through video testimonials, food choices, and various lifestyle issues. HCs present specific chapters in LWD on a tablet computer

along with other visual, low-literacy materials to reinforce specific diabetes self-management concepts. In addition, HCs can utilize available evidence-based tablet computer tools in decision support. HCs are trained on diabetic medical nutrition therapy and basic physical activity recommendations for those with poor mobility so that they can work with patients to set individual goals. Education will address realistic and achievable food choices, portion sizes, cooking preparation, relationships between medications-meals-glucose levels, and integration of movement into lifestyle. HCs routinely identify basic resource needs that they address by facilitating connections with food pantries, free park district activities, or assistance paying utilities. Additional relevant resources are identified using online databases, such as purplebinder.com and healthrx.org.

*Text Messaging.* All text messages will be tailored by health coaches and sent through a custom software application (*mytapp*). [name] developed *mytapp* for community-based health behavior research. *Mytapp* sends messages immediately or at a scheduled date/time, recurrent messages (daily, weekly, or weekdays), group messages, or multiple question surveys. *mytapp* requires a password for access and is restricted to trained research personnel. HCs receive training on *mytapp* and schedule messages for their patients regarding appointments, medications, and goals. The content of text messages will parallel our conceptual framework providing social support, competence, perceived barriers and benefits of treatment, and severity and susceptibility of complications. Health coaches will monitor their own patients' responses for their cohort. Additionally, the project coordinator will monitor all *mytapp* activities including subject responses.

Goals set jointly by HC and patients are SMART (specific, measurable, achievable, relevant, and time-specific). Action plans are culturally tailored to subject individual needs, preferences, and resources. African-American HCs will highlight specific activities and resources in African-American communities. Likewise, Latino HCs include Spanish text messages (if Spanish is the preferred language) and different community-based resources and educational materials. Activity choices may include routine medication use, food choices, physical activity, stress reduction, smoking cessation, or other behavioral targets. Subjects indicate their level of confidence in success to help refine the frequency and intensity of activity through motivational interviewing techniques. HCs will help their patients anticipate barriers, discover potential solutions, and establish follow up plans. They employ problem-solving strategies and engage community resources as needed.

Text messaging will further enhance HCs' ability to support their patients. They will direct messages to maintain motivation, elicit feedback on progress, and screen for barriers that may reduce chance of success. For example, a morning text message may ask a patient how they did on their goal the previous day. Responses may be "yes/no", a rating scale, or other measure of activity. The subject will receive an automated response based on progress made, and additional messages (tips/problem solving messages) if not achieving goals. No more than seven messages will be delivered weekly, except for optional medication reminders.

| Example Text Message Templates |               |                                                                       |
|--------------------------------|---------------|-----------------------------------------------------------------------|
| Message Type                   | Frequency     | Example                                                               |
| Medication Reminder            | 1-4 times/day | "Hi, [name], just checking to see if you took your morning pills." |

|                      |          |                                                                        |
|----------------------|----------|------------------------------------------------------------------------|
| Refill Reminder      | Monthly  | "Make sure you don't run out. Check to see when a pill refill is due." |
| Appointment Reminder | Variable | "Just a reminder that you have a doc's appointment today."             |
| Goal Monitoring      | Variable | "Remember your goal. Did you take your meds last night?"               |
| Glucose Monitoring   | Variable | "Hello, [name], have you had time to check your sugar today?"     |
| Self-Efficacy        | Weekly   | "Taking your meds is within your control. You can do it."              |
| Motivation           | Weekly   | "You have come a long way! Keep up the good work!"                     |

### **Temporary modifications to data collection during COVID-19 pandemic**

Due to the COVID-19 pandemic and social distancing orders, all pharmacist and health coach contact with participants will be made remotely and not in-person. This includes phone calls and Doximity video telehealth.

### **Additional text messaging for mDAS Sub-study Supplement**

Participants in the sub-study will be asked to answer daily questions on their previous night's sleep. They will complete the seven day sleep assessment surveys based on their preference by either text message surveys using myTapp or they will receive a text link to an online-based survey through a secure, web-based data collection application, such as REDCap or Qualtrics. The text messages will serve as a modified mobile consensus sleep diary for patients during the sleep period. The questions will include the following:

- 1) What time did you get into bed last night?
- 2) What time did you try to go to sleep?
- 3) How long did it take you to fall asleep?
- 4) How many times did you wake up, not counting your final awakening?
- 5) In total, how long did these awakenings last?
- 6) What time was your final awakening?
- 7) What time did you get out of bed for the day?
- 8) How would you rate the quality of your sleep? a) very poor, b) poor, c) fair, d) good, or e) very good? Please text the letter that corresponds to you (if using text message response).
- 9) In total, how long did you nap or doze?
- 10) Comments

Thanks for your participation.

### **Transition and Retention**

Despite having "access" to healthcare, participants will be economically vulnerable individuals with uncontrolled diabetes. Ethically, we acknowledge that the "usual care" currently received often does not meet patients' needs or standards of care. Therefore, participants assigned to usual care will receive initial support to engage existing resources available through UI Health, such that healthcare providers will consider this an acceptable alternative upon randomization (clinical equipoise).

Upon randomization, participants will receive referrals to a diabetes educator and clinical pharmacist for medication reconciliation, adherence support, and education. Staff can schedule the visit at data collection. This is important as our prior work with medication reconciliation identified discrepancies in almost 60% of patients. A one-page list of clinic resources with names and direct telephone numbers (e.g., social worker) will be provided so they can more easily navigate the system. Finally, low-literacy, paper-based diabetes education information will be provided. At the end of year 1, these patients will cross-over and receive *mDAS*. Prior to this transition, HCs will work with the patients and their social support network to prepare them for the transition. Participants randomized to usual care will receive *mDAS* for one year.

*Retention strategies.* Participants will be reimbursed \$30 for each data collection. Participants assigned to the intervention in year one will receive an additional \$50 at 6 months and 12 months if they complete at least one videoconference before each data collection. Participants assigned to the intervention in year two will receive an additional \$50 at 18 months and 24 months if they complete at least one videoconference before each data collection. Participants who complete all five data collection visits and videoconferences with the pharmacist as described above will receive up to \$250 for completing the study.

*Additional Retention Strategies for mDAS Sleep Sub-study Supplement* Participants will be reimbursed an additional \$40 for participating in the sleep sub-study and turning in the wrist actigraph.

*Temporary modifications to compensation during the COVID-19 pandemic.* Participants may choose to be paid through their preferred electronic pay app (such as QuickPay/Zelle, Venmo, or Paypal) OR a gift card of their choice from a list of online retailers such as Walmart, Target, Amazon, or Visa. Gift cards will be issued in the amounts as described above for each data collection visit and can be mailed, emailed or texted depending on the vendor.

Due to social distancing orders, participants will have the option to complete their HbA1c and cholesterol profiles using a home test kit. They may also choose to wait and come in to the CRC for a blood draw once research operations resume. Because of the added time and effort required for each of these options, an additional \$20 will be given to subjects for lab tests completed during the COVID-19 pandemic only. This additional incentive will not be offered once in-person interviews and phlebotomy resume.

Other retention strategies include: (1) periodic phone calls/ mailings to verify contact information; and (2) use of alternative contact information. We have developed a comprehensive standardized web-based search protocol that includes five people locators, major social networking sites including those with more minority involvement, and the department of corrections database. Searches are conducted on the target individual as well as alternative contacts.

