### **6.1 Overview of Participant Procedures**

#### Recruitment and Randomization

1. Potential participants will be identified by one of four recruitment methods previously described.
2. RAs will screen patients for eligibility and discuss the study protocol in detail. If the patient is deemed eligible to participate he/she will complete written informed consent and HIPAA authorization.

3. Enrolled participants will schedule an appointment at the UIC Clinical Interface Core (CIC) to complete baseline data collection, which includes a blood draw.
4. Participants randomized to *mDAS* will receive the intervention component in Year 1, while participants randomized to *Usual Care* will receive it in Year 2. RAs will inform participants of assignment.

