#### Usual Care Component

1. Participants will receive contact information for a diabetes educator and a clinical pharmacist for medication reconciliation.
2. Patients will receive a one-page contact sheet with the names and phone numbers of their local healthcare team as well as paper-based, low-literacy diabetes educational information.

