#### Crossover Transition

1. One year after enrollment, the participants receiving *mDAS* will have the intervention components phased out to assess maintenance. The participants in the usual care group during year 1 will receive *mDAS* support for the subsequent year to assess intensification.
2. Coaches will help participants enlist social support and community resources for long term assistance with medications.

3. Coaches may periodically be contacted by disengaged participants during the following year. These communications will be logged.

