### **Primary Outcomes**

Univariate comparisons between the two study groups for outcomes and covariates at baseline will be conducted using chi-square tests for categorical variables, Kruskal-Wallis tests for ordinal variables, and t-tests for continuous variables. Non-normal continuous data will be transformed prior to analysis.

In order to provide comprehensive analysis for  $H_1$ , we will extend the usual analysis of crossover designs by including a longitudinal trend component in the first year. Thus, we can examine the time course (0, 6, and 12 months) as linear or quadratic over the first three

measurements. This will allow us to investigate whether changes are made early, and at what rate they continue through the rest of the time period. This analysis permits the comparison of trends between the two conditions. In addition, we will regard subjects as a random effect and will use Gaussian mixed-model estimation (SPSS MIXED). We can then substitute treatment by period interactions for the carry-over effects, and the model can be reduced in a recommended sequence (first omit carry-over, then omit treatment, finally omit period). SPSS MIXED will also be used to explore patterned covariance structures such as compound symmetry and autoregression along with incorporating time-constant and time-varying covariates, such as health literacy or diabetes distress.

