Sample Size Justification: Sample size calculations are powered to detect change in A1c. The ADA Technical Review of Diabetes Self-Management Education reported that successful education programs achieved reductions of 5-20% in A1c. The UKPDS 35 demonstrated that each 1% absolute reduction in mean A1c is associated with a 21% decrease in risk for any diabetes-related endpoint, a 21% decrease in diabetes-related deaths, a 14% decrease in risk for myocardial infarctions, and a 37% decrease in risk for microvascular complications. Based on our previous studies, we estimated a mean baseline A1c level of 10% with standard deviation of 1.8 and an effect size of  $(1.0/1.8) 0.56$  for Aim 1. The cross-time correlation was estimated to be 0.30 with compound symmetry structure. We adjusted for clustering and assumed an intraclass correlation coefficient (ICC) of 0.01 with five clusters. This yielded a design effect of 1.34. Two-sided alpha of 0.05 and 80% power were assumed. Allowing for 20% drop-out, 220 patients will be required total.

UI Health billing data show there are 7,258 adult African-Americans and Latinos with diabetes. We estimate that approximately half of these patients have an A1c level above 8.0% based on prior study. We anticipate recruiting 6% of the eligible diabetic population. We have successfully recruited a similar size of patients with type 2 diabetes using comparable recruitment methods.

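### As worded, the protocol has health coaches working with usual-care patients before the end-of-Year-1 crossover, so controls could receive part of mDAS before the 12-month outcomes

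*Protocol*

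**What the plan says.** The Transition and Retention text in Section 6 lists what usual-care participants get: referrals, a list of clinic resources and printed education. It then says "At the end of year 1, these patients will cross-over and receive" mDAS. The next sentence is "Prior to this transition, HCs will work with the patients and their social support network to prepare them for the transition". The one after it returns to participants randomized to usual care, who get mDAS for one year.

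Other parts of the protocol describe the control year differently:

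- Section 6.1, Usual Care Component, has two items. The first is "Participants will receive contact information for a diabetes educator and a clinical pharmacist for medication reconciliation"; the second is a contact sheet with printed education. Section 6.0 gives a similar description. Neither mentions a coach.
- Section 6.1, Recruitment and Randomization, says mDAS participants get the intervention in Year 1, "while participants randomized to *Usual Care* will receive it in Year 2".
- Section 6.4, Health Coaches, says "HCs address nine critical content areas over the course of the one-year intervention". Engaging social support is one of the nine.
- Section 6.1, Crossover Transition, first covers both arms (mDAS phased out, usual care starting mDAS) and then says "Coaches will help participants enlist social support and community resources for long term assistance with medications". It names no arm.
- Section 12.0, Primary Outcomes, sets the Year 1 comparison: "we can examine the time course (0, 6, and 12 months) as linear or quadratic".

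**The concern.** The sentence on preparatory coach work stands between two sentences about usual care, and the only transition named there is the usual-care crossover. Staff who follow it literally would contact controls and their support networks before the end of Year 1. That work resembles an active component of mDAS, and it could fall before the 12-month measurement.

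Aim 1 compares A1c, blood pressure, LDL-cholesterol and medication adherence between arms. Part of adherence is self-reported (Section 8.0), and a survey answer can respond to recent coach contact more readily than a laboratory value. If the contact helps, the control arm looks better at 12 months and the Year 1 difference shrinks. The starting point for that arm's own mDAS year also shifts, which affects the Year 2 assessment of intensification.

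**Working it through.** This is a question of text and timing, so the passages are set side by side.

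**1. Which arm does the sentence concern?** In its own paragraph, it concerns usual care: the sentences before and after are about that arm. Two other places point the other way. Crossover Transition has a similar sentence about social support, listed after the mDAS phase-out. Sustainability (Section 12.0) uses the word transition for the mDAS group's return to usual care. Neither place says that the sentence in Transition and Retention belongs to the mDAS arm.

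**2. Does the literal reading conflict with the design?** Yes. Section 6.0 and the Usual Care Component list give controls no coach in Year 1, and Recruitment and Randomization puts their intervention in Year 2.

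**3. Is the contact separated from the 12-month outcomes?** No passage orders it after the 12-month data collection or limits its content. Crossover Transition ties the change to one year after enrollment, not to completion of the 12-month visit. Under the pandemic modifications, participants may also decline home testing and wait for a blood draw until research operations resume. A 12-month A1c could therefore be drawn after coach work has begun, even if the survey was on time.

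**4. Is the contact traceable?** Largely. Coaches complete a standardized form after every participant contact (6.1, Health Coach Component; 8.0, Process Measures). This allows exposure to be identified afterwards but does not prevent it.

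**5. Can the size be computed?** If controls receive a fraction c of the benefit before 12 months, the expected difference falls from 1.0 to 1.0 × (1 − c) A1c points. The document gives no number, length or date of contacts, so c is unknown.

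The starting power is not fixed either. Sample Size Justification says "Two-sided alpha of 0.05 and 80% power were assumed". Its design effect reproduces: 220 × 0.8 / 5 = 35.2 per cluster, and 1 + 34.2 × 0.01 = 1.342. The total of 220 does not reproduce with the usual formula

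N = 4 × f × ((1.96 + 0.8416) / (1.0/1.8))² × 1.34 / 0.8,

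which assumes 1:1 allocation. The factor f depends on the analysis, with correlation 0.30:

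| Analysis | f | N | Power at 220, no dilution |
|---|---|---|---|
| 12-month value only | 1 | 170 | 88.9% |
| Baseline-adjusted | 1 − 0.30² = 0.91 | 155 | 91.6% |
| Change score | 2(1 − 0.30) = 1.4 | 239 | 76.7% |

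The protocol does not name its formula, and 220 lies inside this range, so this does not show that 220 is wrong. It does mean that any figure for lost power would rest on an assumed c and an assumed starting power.

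**The case against.** The strongest reply is that this is a misplaced sentence. Coaches, social support and preparation for a transition all fit patients leaving mDAS, who already have a coach, better than controls, who do not. Several sections start the control arm's intervention only after one year, so coaching controls earlier would contradict them all. Even taken literally, preparation is not mDAS, which consists of monthly home visits, pharmacist videoconferences every other month and text messages over a year. A single preparatory visit, as an illustration, would be 1 of 12 monthly coach visits, without a pharmacist and near the end of the year. Nothing suggests that the 6-month data would be affected.

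Most of this stands. A drafting slip is plausible, and brief, late contact would probably move A1c little. It does not remove the conflict: one reading exposes controls and the other does not, and the protocol gives staff no basis for choosing. The reply about A1c is also weaker for self-reported adherence.

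A reader might infer more than the text supports. One such inference is that the trial plans to give controls the intervention in Year 1; the other sections say the opposite. Another is a specific loss of power, for which the protocol supplies neither the exposure nor a reproducible starting point. A third is that every coach contact must wait for the A1c sample. Scheduling calls carry no intervention content, and a sample deferred under the pandemic provisions could hold back mDAS while the 18- and 24-month visits approach.

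**Conclusion.** The point holds as an internal contradiction with a possible effect on the main comparison. As worded, Transition and Retention has coaches working with usual-care patients before crossover, against the description of usual care elsewhere, and no rule keeps that work after the 12-month outcomes. Actual contamination is not established.

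The direction, toward no effect in Aim 1, rests on the assumption that coach contact helps. The size cannot be quantified from the document. It is probably small for A1c if contact is brief and late, and less certain for self-reported adherence. The correction is cheap and protects the main contrast, so it is worth making.

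**What to change.** Reconcile Recruitment and Randomization, Usual Care Component, Crossover Transition, and Transition and Retention:

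1. State which arm the preparatory sentence concerns.
2. State that usual-care participants receive no coaching or support content from health coaches, scheduling aside, until their 12-month data collection is complete.
3. Where the 12-month blood sample is delayed under the pandemic provisions, record whether it was drawn before or after first coach contact, and examine this in a sensitivity analysis. The contact forms already planned should supply the dates.

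The cost is a few sentences and one derived variable. The downside is that a usual-care patient with a late 12-month visit starts mDAS somewhat later.
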